## Abstract

**Background:**

Adolescence is a period of elevated stress sensitivity, which places adolescents at increased risk of developing mental health problems such as burnout, depression, anxiety, and externalizing problems. Early intervention of psychological needs and low-threshold care addressing such needs may prevent this dysfunctional development. Schools may provide an important environment to identify and address psychological needs. The aim of this protocol is to describe the design of a study aiming to evaluate the effectiveness of low-threshold school-based skills-training programs promoting the mental health of adolescents and to examine moderators of the effectiveness.

**Methods:**

A Randomized Controlled Trial will be conducted to examine the effectiveness of two school-based skills-training programs aiming to promote mental health by improving either skills to deal with performance anxiety or social skills. A multi-informant (i.e., students, parents, and trainers) and multi-method (i.e., questionnaires and physiological measurements) approach will be used to assess program targets (skills to deal with performance anxiety or social skills), direct program outcomes (performance or social anxiety) and mental health outcomes (i.e., stress, internalizing and externalizing problems, self-esteem and well-being), as well as specific moderators (i.e., student, parent and program characteristics, social support, perfectionism, stressful life events, perceived parental pressure, positive parenting behavior, treatment alliance and program integrity).

**Discussion:**

The current study will provide information on the effectiveness of school-based skills-training programs. It is of crucial importance that the school environment can provide students with effective, low-threshold intervention programs to promote adolescents’ daily functioning and well-being and prevent the emergence of mental health problems that negatively affect school performance.

**Trial registration:**

Dutch Trial Register number NL7438. Registered 12 December 2018.

## Background

Adolescence is a phase of rapid growth and development in physical and psychological domains [1]. During adolescence many changes occur simultaneously, including puberty and the transition to high school. At the same time, adolescence is a period of increased stress sensitivity [2–4], which contributes to adolescents’ increased risk for mental health problems, such as burnout, depression, anxiety and externalizing problems [5–8] and which may negatively affect the well-being of adolescents [9–11] and later developmental outcomes [12]. Stress also has a negative effect on academic performance [13–15] and can result in school absenteeism or dropout [16]. Addressing psychological needs at an early stage, for instance to deal with stress and stress-inducing factors, is of crucial importance to prevent the development of mental health problems, school dropout and dysfunction later in life. An environment particularly suitable to help vulnerable adolescents is the school environment. Intervening in the school-context may be particularly beneficial to schools as well-being and mental health have been positively associated with academic functioning [17].

A promising avenue to reach adolescents with psychological needs is by focusing on stress. As experiencing stress is part of normative development during adolescence [4], interventions focusing on the reduction of stress may be experienced by adolescents as a low-threshold and appealing way to address their psychological needs. Stress has been defined as the condition or feeling that results when individuals perceive that the demands of a situation exceed the individual’s personal, psychological, or social resources [18]. During adolescence, performance pressure as well as social situations at school may trigger feelings of stress, also referred to as academic and social stress [19].

Academic stressors that are frequently reported by adolescents are related to tests, grades, homework, expectations about school, expectations about their career and future life plans [20]. Academic stress is related to performance anxiety, where individuals experience fear of failure, the fear to be unable to meet certain expectations of themselves or others, or test anxiety. Improving skills to deal with academic stress through intervention programs can reduce stress in the school environment [21, 22]. Social stressors originate from an individual’s social environment and are caused by factors that disrupt the relationship with others, such as social rejection, isolation, disagreements or bullying [23]. Dysfunctional social interactions can trigger stress [24], hence, improving social skills by teaching adolescents to better communicate with others, might reduce perceived social stress.

The ability to cope with stress is very important and requires cognitive and behavioral efforts to control or reduce stressful experiences [25]. One way to thus counter the negative effects of adolescents’ stress is addressing either academic or social stress by offering preventative skills-training programs that provide adolescents with tools to effectively cope with stress and regulate emotions [26]. In order to effectively help adolescents who perceive academic or social stress and to promote their mental health, this protocol describes a study to examine the effectiveness of two school-based skills-training programs targeting skills to deal with performance anxiety or social skills.

Several studies implemented skills-training programs targeting performance anxiety, mainly focusing on test anxiety. Recent studies in secondary school students reported decreased test anxiety compared to controls after interventions targeting a combination of coping skills, relaxation techniques and study skills [27–31]. A reduction was also found in physiological stress [27, 31], internalizing problems [28] and behavioral problems [27], as well as increased self-esteem [27].

Recent studies demonstrated increased positive social behavior and improved social skills in secondary school students after mindfulness or social and emotional skills based interventions compared to controls [32, 33]. A reduction was found for perceived stress [32], problem behaviors [33, 34] and internalizing problems [35], as well as increased self-esteem [33–35].

In sum, previous studies targeting skills to deal with performance anxiety and social skills in secondary school students demonstrated promising results, for academic and social stress as well as for mental health outcomes. However, previous research shows several limitations. First, only few studies performed a randomized controlled trial (RCT) [30, 35], which means that in non-randomized studies there might be confounding factors or bias. Second, only few studies used a targeted small-group intervention [28, 30, 35], which means that in studies with universal interventions there might be minimal or no effect for at-risk students because their greatest effect is on low-risk students, who are not the desired target [36]. Moreover, these studies had relatively small sample sizes (*N* = 74 and *N* = 56) [30, 35] which precludes clear conclusions about the effects, or targeted youth that experienced a traumatic event [28], precluding conclusions about non-clinical community samples. Third, only a few studies investigated mixed-samples of students from diverse ethnic backgrounds [30, 31, 33], which is important to be able to draw conclusions that generalize to the whole population [37]. Hence, there is still insufficient evidence for the effectiveness of skills-training programs, especially for students in mixed-ethnicity community samples. Additionally, little is known about potential moderators of the effectiveness of school-based skills training programs, likely due to power issues. Which students benefit from such training programs and which factors contribute to their effectiveness?

Moderators are student, parent and program characteristics that are likely to affect the effectiveness of the training programs. Student characteristics that may affect the effectiveness of the skills-training programs include demographic characteristics (i.e., age, gender, ethnicity, educational level and socioeconomic status (SES)) and social support, perfectionism, stressful life experiences, severity of problems, perceived parental pressure and basal stress levels.

For instance, high levels of social support have been positively associated with well-being and mental health in children and adolescents [38, 39]. Moreover, high levels of social support have been associated with a more beneficial psychological treatment outcome in clinical samples [40, 41]. High occurrence of stressful life events has been associated with stress-related psychopathology and negative mental health outcomes, such as anxiety, depression and risk behavior [42–44] and predicts adverse treatment outcome [45]. On the one hand, high social support and low occurrence of stressful life events are associated with more beneficial outcomes. On the other hand, several studies showed larger program effects for adolescents with high initial problem severity [46, 47]. Following this line of reasoning, it may also be possible that students with low social support or with high occurrence of stressful life events profit most from the skills-training programs, because the sessions provide them with tools that are not provided by their social network.

Perceived stress positively correlates with perfectionism [48] and perceived parental pressure [49], which have been associated with mental health problems such as anxiety and depression [50–52]. Previous studies showed that perfectionism and maternal rejection (i.e., less emotional warmth), the latter associated with parental pressure [52], are related to less beneficial treatment outcomes in children and adolescents with anxiety or depression [53–56]. It is therefore expected that students with higher levels of perfectionism or students who perceive more parental pressure may benefit less from the skills-training programs.

Parent characteristics that may affect the effectiveness of the skills-training program include demographic characteristics (i.e., educational level) and positive parenting behavior. Positive parenting behavior increases adolescents’ social competence reflecting positive functioning at school including peer competence and attachment to school [57], and improves the relationship between parent and adolescent [58]. Because of this warm relationship, parents may be more involved in the life of their child and students may feel more confident to talk about the program at home. It is therefore expected that the skills-training programs are more effective for students with parents that show more positive parenting behavior.

Additionally, program characteristics, i.e., treatment alliance, program integrity and trainer characteristics such as ethnicity, experience and perceived competence, may moderate the effectiveness of the skills-training programs. Treatment alliance is the perceived bond between the participant of the skills-training program and the group leader (i.e., trainer), which is demonstrated to be positively associated with treatment outcome in depressive patients [53] and in children and adolescents with anxiety disorders [59, 60]. Hence, it is expected that high participant-trainer alliance contributes to a more beneficial outcome. Program integrity refers to the extent to which a program is implemented as originally planned, and is reported by very few studies [61]. Finding non-significant effects may not be caused by an ineffective program, but because a program is not carried out as intended [62]. Therefore, it is important to examine program integrity in order to correctly draw conclusions on the effectiveness of the skills-training programs.

In sum, the current protocol describes a study that will be conducted to examine the effectiveness of two types of targeted school-based skills-training programs addressing skills to deal with performance anxiety (program 1) and social skills (program 2). In order to overcome some of the limitations of previous studies, small-group skills-training programs are evaluated in a mixed-ethnicity community sample of students with different educational levels, where students self-select to one of the skill-training programs. For each program, a RCT is performed to examine if these low-threshold interventions reduce performance or social anxiety and promote students’ mental health. Both skills-training programs will be compared to a control waitlist condition. As illustrated in Fig. 1, it is expected that the performance anxiety skills-training program will improve skills to reduce performance anxiety (i.e., coping skills, including negative thought restructuring and managing emotions), resulting in a reduction in students’ performance anxiety (i.e., fear of failure and test anxiety) and in improved mental health (i.e., reduced stress and internalizing and externalizing problems, and increased well-being and self-esteem). Additionally, we expect that the performance anxiety skills-training program will directly reduce performance anxiety and improve mental health. It is expected that the social skills-training will improve students’ social skills and thereby reduce their social anxiety and improve their mental health (i.e., reduced stress and internalizing and externalizing problems, and increased well-being and self-esteem). In addition, we expect that the social skills training program will directly reduce social anxiety and improve mental health (see Fig. 1). The second aim is to investigate the moderators of the effectiveness of both skills-training programs on all outcomes. This is important because it is likely that the skills-training programs are not equally effective for all students. Student, parent and program characteristics will be examined as potential moderators. The final aim of this study is to evaluate if the school-based skills-training programs are experienced as sufficiently accessible, meaningful and helpful by the students, their parents and the trainers. Figure 1 shows a conceptual model of the research design.

**Fig. 1 Fig1:**
[figure not shown]
Conceptual model of the research design

## Methods/Design

### Design

A RCT will be conducted for both school-based skills-training programs targeting: 1) skills to deal with performance anxiety and 2) social skills. For each skills-training program, students who have indicated interest in attending a training at their school, will be randomized by the first author (stratified for education level) into the experimental group in which the training starts immediately or into a waitlist control group that receives the training approximately eight weeks later (see Fig. 2), using computerized randomization in a 1:1 ratio. We will use a multi-method (questionnaires and physiological data) and a multi-informant (students, parents and trainers) design and will recruit a mixed-ethnicity sample of students from different educational levels.

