### Study sample

For each school-based skills-training program we aim to include *N* = 130 students to ensure there is enough power for the analyses (*N* = 65 for both the experimental and waitlist control group). A total of *N* = 260 students will be included. This sample size is sufficient to investigate the effectiveness of the interventions and potential moderators, with a power of .80, an alpha of .05 and a medium effect size of .25 [63].

Participants are mixed-ethnicity students in the first, second, and third year of secondary schools (7th, 8th and 9th Grade students) of at least three schools in the Netherlands that offer education at various levels (from vocational education level to preparatory university education level). The students will be between 11 and 16 years old.

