### Recruitment

#### Schools

So far, three Dutch urban secondary schools have been recruited. Possibly, additional schools will be recruited via the researchers’ contacts and networks. Schools that show interest will receive information about the study and will be asked to participate.

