#### Participants

This study will be performed in the context of a Response to Intervention model (RTI) that aims to identify vulnerable students and provide them with appropriate interventions [64]. Before entering the current study, focusing on the effectiveness of school-based skills-training programs, classes of students receive educative information about stress and are asked about their own stress levels (i.e., Tier 1 of the RTI model: universal intervention targeting all students). After these three educative lessons, students will be asked to indicate if they would like to learn more about dealing with academic or social stress by following a skills-training program. Students will be asked to self-select to one of the school-based skills-training programs (i.e., skills to deal with performance anxiety or social skills), if needed assisted by parents or teachers (i.e., Tier 2 of the RTI model: targeted intervention directed at self-selected at-risk students). Students who self-select to a Tier 2 intervention are asked to participate in the current study.

The skills-training programs are offered by schools via their own care system or by external youth care organizations. The interventions are implemented at school by trained teachers or professionals. Students and parents receive written information about the different skills-training programs that are offered and receive an information letter about the corresponding research study. Trainers also receive an information letter about the study. Students and parents will be asked to provide active informed consent for the student’s participation in the study. If students or parents do not give consent to participate, the student will not receive the skills-training program offered by the study but will receive help via the schools’ own care system. Active informed consent will also be obtained from parents and trainers for their participation. After receiving consent, students will be randomized into the experimental condition or the waitlist condition. Figure 2 shows the flow chart of the design of the study.

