Third, a challenge in this study is to implement the skills-training programs at schools because of logistics (i.e., different locations and scheduling) and the participation and involvement of multiple parties (i.e., researchers, schools, students, parents, youth care organizations that provide the skills-training programs, and municipalities involved). With regard to the latter, multiple schools and multiple organizations offering skills-training programs are involved in this study. To strengthen the collaboration between the schools and the youth care organizations, we will organize regular meetings with all parties involved and aim to match the schools with suitable youth care organizations. With regard to logistics, it is very important that enrollment in the skills-training programs and arrangements in terms of schedules and locations will be timely communicated with the schools and youth care organizations. The researchers will try to overcome potential implementation issues by being present at the schools at least once a week, by giving weekly updates to the youth care organizations, and by being available for consultation at any time during the referral process and skills-training programs.

Fourth, the participating schools do not belong to the same municipality geographically, which complicates the financial conditions for the skills-training programs. To overcome financial issues, we will talk to different municipalities to obtain funding for the skills-training programs. Finally, it is important to be aware that in the Netherlands, school and youth care systems are completely separate, both organizationally as well as financially, which makes cooperation complicated. We try to overcome this challenge by giving regular updates and organize meetings with all parties involved, to promote a fruitful collaboration.

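### Randomisation is stratified by education level only and the ANCOVA adjusts for baseline only, although training is organised school by school; adding school to both would balance the arms and training groups and modestly improve precision.

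*Protocol article*

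**What the plan says.** Under Design, students in each programme's trial "will be randomized by the first author (stratified for education level) into the experimental group in which the training starts immediately" or into a waitlist group trained about eight weeks later, "using computerized randomization in a 1:1 ratio". No other stratum is named. The students concerned are "students who have indicated interest in attending a training at their school". Under Statistical analyses, the only covariate named for the ANCOVAs is the pre-test value of the outcome; moderators are added in further models.

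Other sections show how far delivery depends on the school:

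- **Number of schools.** Study sample: participants are students "of at least three schools in the Netherlands that offer education at various levels". Schools: "So far, three Dutch urban secondary schools have been recruited", with more possible.
- **Place and format.** Interventions: weekly small-group sessions at the student's school. No group size is given.
- **Trainers.** Participants: "The interventions are implemented at school by trained teachers or professionals". The programmes come through the school's own care system or external youth care organisations.
- **Organisations.** Discussion: "multiple schools and multiple organizations offering skills-training programs are involved in this study", and the researchers "aim to match the schools with suitable youth care organizations". The same section lists differing locations and scheduling as a logistical challenge and says that the schools are not all in one municipality.

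**The concern.** School is the level at which the student mix, the trainer, the location and the training calendar can vary. T2 is tied to completion of the training in the experimental group (Data collection), so its date can also vary by school. Education level is a different factor: the schools offer several levels, so balancing on level does not by itself balance on school.

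Three things are at stake:

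1. School mix can differ between arms by chance. The baseline covariate takes up part of any stable difference between schools, but not a difference in change from T1 to T2.
2. Variation between schools that the model omits stays in the error term and costs some precision.
3. The students allocated to immediate training at a school become its training groups. An uneven split within a small intake gives groups of uneven size in a programme meant to be delivered in small groups.

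**Working it through.** **Inputs from the protocol article.** N = 130 per programme, 65 per arm; power .80, alpha .05, effect size .25 (Study sample); at least three schools; 1:1 allocation stratified by education level (Design).

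**Assumed, because the article does not give them.** Three schools of equal size; three education levels, unrelated to school; permuted blocks of 4 within level; intake sizes of 10 to 20; a school effect with intraclass correlation (ICC) of 0 to 0.10 in the outcome as analysed. The error-rate simulation has no separate baseline covariate.

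**Step 1: the plan's own figure.** Read .25 as Cohen's f, so d = 0.5. For two groups and one covariate, power comes from the noncentral F distribution with 1 and N − 3 degrees of freedom and noncentrality N·f². At N = 128 power is 0.801, and at N = 130 it is 0.808. The planned size is reproduced.

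**Step 2: school imbalance between arms.** If level is unrelated to school, the between-arm difference in one school's share has standard deviation of about √[p(1−p)(1/65 + 1/65)]. With p = 1/3 this is √(0.2222 × 0.03077) = 0.083, or 8.3 percentage points; the simulation gave 8.4. For the largest gap over the three schools:

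| | Level only | School × level |
|---|---|---|
| Median gap | 9.2 points | 2.6 points |
| 95th percentile | 20 points | 4.6 points |
| Gap ≥ 10 points | 45% | about 0% |
| Gap ≥ 15 points | 16% | about 0% |
| Gap ≥ 20 points | 5% | about 0% |

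With four or six schools under level-only stratification, the chance of a gap of 10 points or more is 47% or 51%.

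**Step 3: splits within an intake.** If allocation inside one school intake behaves like a fair coin, the number trained is Binomial(n, ½).

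- n = 10: 2:1 or worse needs 7 or more on one side: 2 × 176/1024 = 34%.
- n = 12: 8 or more on one side: 2 × 794/4096 = 39%.
- n = 16: 21%. n = 20: 12%.

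**Step 4: error rate and power** (d = 0.5, N = 130, 3000 runs per setting; simulation error about 0.004 for type I error).

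| ICC | Design and model | Type I error | Power |
|---|---|---|---|
| 0 | level only, no school term | 0.054 | 0.80 |
| 0 | school stratum and school term | 0.046 | 0.80 |
| 0.05 | level only, no school term | 0.051 | 0.82 |
| 0.05 | school stratum and school term | 0.046 | 0.84 |
| 0.10 | level only, no school term | 0.055 | 0.82 |
| 0.10 | level only, school term | 0.050 | 0.85 |
| 0.10 | school stratum, no school term | 0.041 | 0.82 |
| 0.10 | school stratum and school term | 0.048 | 0.86 |

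**Step 5: hand check at ICC 0.10** (total variance 1).

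- With a school term the residual variance is 0.90, so SE = √(4 × 0.90/130) = 0.166 and power ≈ Φ(0.5/0.166 − 1.979) = 0.85.
- Without it, three school effects add on average 0.10 × 2/3, giving variance 0.967, SE = 0.172 and power 0.82.

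The simulated 0.86 is therefore slightly generous; 0.84 to 0.86 is a fair range. The precision gain comes almost entirely from the school term in the model. Stratification supplies the balance.

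**The case against.** The strongest reply is that this is a design preference with no harm to the inference. Much of that stands. Chance imbalance under valid randomisation is not bias, type I error is 0.051 to 0.055 without any use of school, and power stays at 0.80 to 0.82. If ICC is 0, nothing is gained in power.

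A reader might also infer stronger claims that the article does not support:

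- **Each school has its own provider.** The article reports several organisations and an aim to match them to schools. It does not say that every school has a different one.
- **One arm could be loaded with one school's provider.** Waitlist students have no training before T2 (Waitlist-control group), so provider exposure cannot be unbalanced in that arm. Only school mix, and with it the timing of measurement, can be.
- **T2 falls in a test period at some schools.** No test period is mentioned. Both arms complete the same pre- and post-measurements, and the waitlist is trained straight afterwards, so within a school they are measured around the same training round.

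Two further objections limit the size of the point. The article may describe draws that are in fact made school by school, since students sign up for training at their own school and are randomised after consent. And if education level and school are strongly linked, the existing stratum already balances part of the school mix.

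What does not stand is that this is only detail left to a fuller document. The article itself names the stratification factor and the covariate, and neither is school.

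**Conclusion.** The point holds as an inexpensive design improvement, not as a flaw that threatens validity. Nothing here calls the stated sample size, power or error rate into question. What is left to chance is the school mix of the arms (a gap of 10 points or more in about 45% of allocations, 20 points or more in about 5%) and the size of training groups (about a third of 10-to-12-student intakes at 2:1 or worse). Using school in both the randomisation and the model raises power from about 0.82 to 0.84–0.86 at ICC 0.10 and leaves it unchanged at ICC 0.

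The imbalance figures assume equal schools, level unrelated to school, and draws pooled across schools. The intake sizes and ICCs are also assumed. Imbalance would be smaller if level and school are linked, and largely absent if allocation is already balanced within each school intake.

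**What to change.** 1. For each programme, randomise within school, by permuted blocks or one balanced draw; where a school has separate intakes, do this per intake.
2. Keep education level as a second stratum only where cell sizes allow. School by level gives about 130/9 = 14 students per cell with three levels. Crossing three schools, four intakes and four levels would give 130/48 ≈ 2.7, which is too thin.
3. Include school and education level as fixed factors in the ANCOVA beside the baseline value. Make this change together with the first: stratifying on school without adjusting for it brought no gain in power (0.82 at ICC 0.10), and type I error there was 0.041.
4. If allocation is already run per school intake, state this; only the analysis change then remains.

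The cost is a change to the randomisation settings, a sentence each under Design and Statistical analyses, a few degrees of freedom, and slightly looser balance on education level in very small intakes. N stays at 130 per programme.

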### Statistical analyses

To examine the effectiveness of the skills-training programs, the effects of all outcome measures will be investigated by conducting analyses of covariance (ANCOVAs). The dependent variables are the outcome measures at post-test (program targets, direct program outcomes and mental health outcomes), the independent variables are the conditions and the covariates are the pre-test (baseline) measurements of the outcome measures. The effect of potential categorical and continuous moderators on the effectiveness of the skills-training programs on the specific goals of the programs and mental health of students will be examined by adding the moderators to the ANCOVAs. Data will be imported from an online server software (i.e., Qualtrics) and will be securely stored at the server of Utrecht University where data back-ups will be performed regularly.

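### Randomisation is stratified by education level, but the stated effectiveness ANCOVA adjusts only for the pre-test; adding the stratum would cost almost nothing and could recover a little precision

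*Protocol article*

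**What the plan says.** Under Design, the protocol article says that for each program students are "randomized by the first author (stratified for education level) into the experimental group" or to a waitlist, "using computerized randomization in a 1:1 ratio". The number of strata and any blocking within them are not described. Study sample says that the participating schools' levels run "from vocational education level to preparatory university education level".

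Under Statistical analyses, the effectiveness model is set out term by term. The dependent variable is the post-test score. For the rest, "the independent variables are the conditions and the covariates are the pre-test (baseline) measurements of the outcome measures".

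Education level appears elsewhere in one other analytic role. The Background lists it among the candidate student moderators: "demographic characteristics (i.e., age, gender, ethnicity, educational level and socioeconomic status (SES". The effect of moderators "will be examined by adding the moderators to the ANCOVAs", as a separate step serving the study's second aim. Data collection and the Moderators section both say that education level is recorded at baseline.

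**The concern.** Balancing the arms on a prognostic factor removes that factor's contribution from the true sampling variance of the treatment difference. A model that leaves the factor out still counts its contribution as residual noise. The reported standard error then exceeds the true one, the confidence interval is too long and the test rejects too rarely under the null. Including the factor brings the standard error back in line with the design.

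The article states the covariate set rather than staying silent on it, so this is a stated choice and not a detail left for a fuller analysis plan. At stake is a small amount of precision in the main comparison of each program. Freedom from bias and protection against false positives are not at stake.

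**Working it through.** **Inputs from the article.** N = 130 per program, 65 per arm, power .80, alpha .05, effect size .25 (Study sample); 1:1 allocation stratified by education level (Design); condition and pre-test as the only model terms (Statistical analyses).

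**Assumptions, because the article gives no figure.** Residual R², the share of post-test variance that education level explains once the pre-test is in the model: 0 to .10. Strata: 3 or 4. Allocation within strata: blocks of 4, with simple randomisation as the alternative.

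**1. The plan's own sample size.** Read .25 as Cohen's f. For two groups and one covariate, power comes from the noncentral F with λ = f²N and N − 3 error degrees of freedom.
- N = 130: λ = .0625 × 130 = 8.125, 127 error df, power .808.
- N = 128 is the smallest total that reaches .80.

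The stated 130 reproduces. Reading .25 as Cohen's d would need 252 per arm, and reading it as f² would need 34 in total, so only the f reading fits.

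**2. Size of the mismatch under within-stratum balance.** When the stratum is omitted, the model SE is too large by the factor 1/√(1 − R²). Type I error is approximately 2 × [1 − Φ(1.96/√(1 − R²))].

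| Residual R² | SE too wide by | Type I error |
|---|---|---|
| 0 | 0% | .050 |
| .02 | 1.0% | .048 |
| .05 | 2.6% | .044 |
| .10 | 5.4% | .039 |

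**3. Power, like with like.** The before and after figures must both assume balance within strata, because balance makes the estimate less variable even when the model ignores the stratum. With f = .25 (d = .5), the expected test statistic is .5/√(4/130) = 2.850 and the critical value on 127 df is 1.979.
- Stratum omitted: Φ((2.850 − 1.979)/√(1 − R²)).
- Stratum included: noncentral F with f/√(1 − R²).

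| Residual R² | Omitted | Included | Gain |
|---|---|---|---|
| 0 | .808 | .807 | none |
| .05 | .814 | .827 | 1.3 points |
| .10 | .821 | .846 | 2.5 points |

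**4. Simulation check, N = 130, 4 strata, blocks of 4.** Two simulations with these settings agree.
- R² = .05: type I error about .045 with the stratum omitted; power .810 to .824 in one and .809 to .825 in the other.
- R² = .10: type I error .038 and .041; power .826 to .852 and .824 to .851. The mean model SE was .176 against a true SD of .167 to .168, about 5% too wide.
- R² = 0: no difference.
- Including the stratum restored a type I error of about .05 throughout.

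The largest simulated gain is .851 − .824 = 2.7 points.

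**5. Simple randomisation.** The model SE without the stratum then matches the true variability (R² = .10: .1765 against .1777; type I error .053, within simulation error of .05). Adding the stratum moved power from .803 to .836 at R² = .10, from .797 to .804 at .05, from .804 to .801 at .02, and from .799 to .789 at 0. So without enforced balance, adjustment pays once the factor is moderately prognostic and costs about one point if it is not prognostic at all.

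**The case against.** The strongest objection is that the consequence rests on quantities the article does not give. The pre-test on the same instrument absorbs stable differences between education levels, so the residual R² may be close to zero, and then nothing is lost. The claim that standard errors are too wide also needs balance within strata, which is not described. Both points stand, and they are why the size is given as a range starting at zero. In reply to the second, stratification without any restriction within strata amounts to simple randomisation, so the word has a practical effect only if allocation is balanced.

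Education level will also enter some moderator models. That is true, but those models answer a different question; the main effectiveness estimate still comes from the model without it.

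A reader might infer that the trial's tests will be conservative overall. The article does not support that. Sessions are delivered in small groups and the stated model has no clustering term, which pulls the other way. With groups of 8 in the trained arm only and an intraclass correlation of .05 (both assumptions), the variance factor is ((1 + 7 × .05) + 1)/2 = 1.175, so the model SE would be 1/√1.175 = .92 of the true one, about 8% too narrow. The figures here isolate the stratum and do not predict the net error rate.

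A reader might also infer that power is inadequate without the adjustment. It is not: 128 are needed and 130 are planned. Nor does the article say whether .25 is before or after pre-test adjustment. If before, a pre-post correlation of .5 (assumption) gives f = .25/√.75 = .289 and power of about .90.

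Finally, it is tempting to ask for school as a further factor. The stratification argument does not reach that far, because school is not a stated stratification factor.

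**Conclusion.** The mismatch between randomisation and analysis is real and rests on two explicit statements. Its effect is modest and conditional. If education level is prognostic beyond the pre-test and allocation is balanced within strata, an assumed residual R² of 0 to .10 makes standard errors 0% to about 5% too wide, takes type I error from .05 down to about .04, and forgoes 0 to about 2.7 points of power at N = 130. Under simple randomisation the standard error is valid and only precision is at issue. Considered alone, the omission introduces no bias, adds no false positives and does not breach the planned power. It is worth correcting because the data are already collected and the correction is nearly free.

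**What to change.** In Statistical analyses, state that education level, coded in the strata used for randomisation, is a fixed factor in the main effectiveness ANCOVA for every outcome in each program, and that it stays in the moderator models. Where the physiological outcomes are analysed in about 40 students per program, allow sparse strata to be collapsed by a rule fixed in advance. One sentence under Design on the number of strata and how balance within them is achieved would settle which of the two cases above applies.

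The cost is one clause and two or three degrees of freedom with 3 or 4 strata. At N = 130 with balanced strata and no prognostic value at all, power is .807 instead of .808. In the subsample of about 40, error degrees of freedom would fall from 37 to 35 or 34, which is why collapsing should be permitted there.
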